## Abstract

Worldwide, injuries due to falls in the home impose a substantial burden and merit considerable effort to find effective prevention measures. The current study is one of very few randomized controlled trials that assess the effectiveness of home modification for preventing falls. It is the first carried out with a minority or indigenous community and focused on reducing inequities. Just over 250 households in Aotearoa, New Zealand, with Māori occupants were recruited in two strata, 150 from the Wellington region and 100 from the Taranaki region. These were randomly allocated to equally sized treatment and control groups within the respective regions, the treatment group receiving a package of home modifications designed to prevent falls at the start of the study, and the control group receiving the package at the end of the study. Injury data came from the Accident Compensation Corporation, a state-owned no-fault injury insurer. This provided coverage of virtually all unintentional injuries requiring medical treatment. Matched injury claims were made available for analysis once all identifying fields had been removed. These data will be pooled with data for Māori households from the already-conducted Home Injury Prevention Intervention (HIPI) study, which tested an identical intervention on the general population. In the analysis, the primary outcome measure will be fall injury rates over time, comparing treatment and control households, adjusting for the stratum and prior falls in the household. A secondary measure will be the rates of specific injuries, which are most likely to be prevented by the package of modifications tested. We anticipate that the findings will provide robust evidence for effective injury prevention measures that can reduce an important contributor to health inequities for indigenous populations such as the Māori.

## 1. Introduction

Globally, 1.4% of disability-adjusted life years (DALYs) due to disease and injury in 2010 were from fall injuries, which were the third most important injury type following road injury and self-harm [1]. In New Zealand, falls accounted for 2.9% of DALYs, which was only slightly less than road injuries (3.1%) [2]. Between 2014 and 2016, there was an average of 544 unintentional deaths due to falls per year [3]. Between 2014 and 2018, in a population of 5 million there were more than 24,000 hospitalizations annually for unintentional fall injuries [3] and according to data provided by the Accident Compensation Corporation (ACC), between 2011 and 2018, there were an average of 658,000 falls annually requiring some form of medical treatment, of which more than half were at home (where the setting was defined).

Given the importance of the home as a setting for falls, the home environment is a potential focus of prevention efforts to install safety features or to remove hazards. However, randomized controlled trials focused on the safety benefits of home modification are rare. A meta-analysis of such trials found that home safety assessments, with subsequent modification, were effective in reducing the rate of falls among older people living in the community (rate ratio 0.81, 95% confidence interval (CI) 0.68 to 0.97; 6 trials; 4208 participants) [4]. Our previous study, the Home Injury Prevention Intervention (HIPI) randomized controlled trial, found a reduction in home fall injury rates of 26% (95% CI 6–42%) [5], although the study was not powered to look at specific groups, such as the Māori, the indigenous people of Aotearoa, New Zealand. As Māori suffer from poorer health on average than other New Zealanders, measures that may potentially reduce health inequalities, such as home modification to reduce fall risk, need to be identified. The aim of the current study was to assess the safety benefits of home modification specifically for Māori. The trial was designed to generate evidence for intervention that could be rolled out as a national programme.

Outcomes studied when assessing fall prevention measures are often problematic as they require self-report of incidents, a measure that is subject to various recall-related issues that potentially affect the estimate of effectiveness [6]. A relatively complete record of medically-treated injuries avoids many such limitations. New Zealand has a national no-fault personal injury insurer, the Accident Compensation Corporation (ACC). ACC covers most of the treatment costs for injuries (regardless of fault) provided by doctors, dentists, physiotherapists, specialists, counsellors and other health professionals and 80% of lost earnings apart from the first week absent from work. Where the co-payment provided by ACC is insufficient to cover costs, the patient pays an additional surcharge. Although the ACC data provide a near-complete set of records of injuries requiring some form of medical or dental treatment, lower levels of access to medical treatment can lead to lower claim rates that underrepresent the underlying injury rates, as has been noted for Māori, for example [7]. Despite these minor limitations, ACC data provide a highly suitable outcome measure (counts of injuries receiving medical attention) to test the hypothesis that occupants of homes receiving the package of modifications will have a lower rate of home fall injuries over a subsequent two-year period.

## 2. Materials and Methods

### 2.1. Methods and Design

#### 2.1.1. Study Design

The Māori Home Injury Prevention Intervention (MHIPI) is a single-outcome randomized trial. The injury data to be analyzed are anonymized and the household is the unit of analysis. The household consists of all people who nominate the included household address as their home address. A secondary analysis will look at the odds of home fall injuries compared to other home injuries, which will account for age, which was found to be important in the analysis of the previously conducted HIPI study [5].

Ethical approval has been provided by the Massey University Human Ethics Committee (reference 4000022369).

#### 2.1.2. Target Population and Sampling

Participants were recruited by community providers from households in the Wellington and Taranaki Regions of New Zealand, some of whom recently received government-subsidized home insulation retrofitted to their homes, and others recruited from networks provided by iwi (Māori tribal groups), direct advertising in community newspapers, presentations to community groups and events, as well as personal contacts. To qualify for the study, houses needed to have at least one occupant who identified as Māori. Only those people who stated they intend to live at that address for the subsequent three years were eligible for participation, as the study seeks to evaluate the safety benefits of home improvements over that period. Only owner-occupiers were approached, as people renting houses tend to be a very mobile population in New Zealand, which does not suit the aims of the study. There were no other qualifying criteria (such as age, sex, health, previous falls, etc.). Two community trusts that mainly undertake insulation retrofitting recruited participants: WISE–Better Homes in Taranaki and the Sustainability Trust in Wellington. Following consent to be part of the study, which was obtained by the community trusts, 254 households were randomized to treatment and control groups by an Otago University statistician (see Figure 1).

## 3. Procedure

### 3.1. Home Modifications

A qualified builder assessed each house in the intervention group using a checklist to identify any hazards in the home that were within the scope of the treatment provided. The modifications done in the intervention houses over a 10-month period between December 2013 and October 2014, consisted of (where necessary): handrails for steps and stairs; some other minor repairs to steps; grab rails for bathrooms and toilets; provision of outside lighting; high-visibility and slip-resistant edging for outside steps; fixing of lifted edges of carpets and mats; non-slip bathmats; and slip resistant surfacing for outside surfaces such as decks. Where needed, smoke alarms were also installed, but are not relevant to the outcome measure. The same process was used for households in the control group once the study was completed, from late 2016 to early 2017. The average cost per house modified was approximately $NZ500. A 10% sample of households was contacted following the repairs to ensure that the treatment had been carried out as expected. All these households reported that the interventions were undertaken as specified in our records.

### 3.2. Outcomes

The primary outcome is rates of medically-treated unintentional falls per household per year. Secondary outcomes are medically-treated specific injuries (injuries that are potentially prevented by the treatment applied—see further details below) and costs of both these types of injuries, due to falls generally or due to the specific injuries. Costs are those borne by the health insurer, the ACC, as described above. Injury costs in relation to intervention costs will be analyzed to inform cost-benefit analyses of the intervention.

Rates will be estimated, firstly, for the MHIPI participants by themselves and, secondly, for the MHIPI participants plus all the Māori household members of the HIPI study, which shared an almost identical intervention. One important difference was that participants in the HIPI study consented to have the study team access their ACC injury records, which were assigned to individuals. To be consistent with the MHIPI data analysis, data for the Māori household members of the HIPI study will be aggregated to the household level.

A sensitivity analysis will be conducted of the odds of falls and the odds of specific injuries compared to all other medically treated home injuries. This will enable models to be fitted that control for age group, which was found to be an important factor in the analytical models used in the analysis of the HIPI study [5]. Such an analysis will lose a proportion of information compared to the primary analysis of injury rates because households without any home injury claims over the assessment period do not contribute data. As the current intervention being tested was designed to prevent injuries arising from falls, it can be assumed that other types of injuries that occur in the home (burns, scalds, poisoning, cuts, stings, strains, collisions, etc.) would be relatively unaffected by the intervention. Using an odds ratio as an outcome measure has the additional benefit of controlling for propensity to seek—or to be differentially referred for—medical treatment following an injury, which is known to vary between different population groups, and to be lower for Māori than for others [7]. As randomization was carried out at the household level and stratified only at the regional level, there is always the potential for the intervention and control groups to differ at random, according to important characteristics associated with fall rates, such as age. Analysis of the odds of a particular injury type or mechanism compared to other injury types or mechanisms, is common in road safety for the assessment of vehicle-related safety characteristics, for example [9].

In order to detect a change of 26% in the percentage of households with medically-treated injuries arising from falls (α of 0.05, 80% power), we calculated that a sample size of about 125 households in each of the two arms of the study (treatment and control groups) would be required.

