#### 3.3.2. Estimating Injury Rates

In the HIPI study [5], participants consented to researchers analyzing their ACC injury records as a condition of being part of the study, and these were provided by ACC for the analysis. For the MHIPI study, ACC provided anonymized injury records matched to addresses we supplied to them and all household members were potentially part of the study. The ACC injury data included the age group and sex of the claimant as well as an address identifier that was matched to information on the treatment arm and details of the modification applied once address information had been removed. Therefore, we cannot estimate fall injury rates per person-time as we have no adequate denominators. Instead, we will estimate injury rates at the household level. Although the data were anonymized for the MHIPI study, meaning that the total number of people whose injuries were potentially being assessed from the anonymized address lists was unknown, the mean number of consenting participants per household from the HIPI study was 2.2 overall, 3.1 for Māori and 2.1 for non-Māori households.

The treatment effect will be estimated by the SAS [11] procedure GENMOD by fitting a Poisson model with a log link function to injury counts at the household level with an offset that is the log of the length of the time interval over which the injury count was obtained. As with the HIPI study, where prior falls were an important predictor of falls during the trial period, a covariate in the model would be a count of fall injuries in the 365 days prior to the start of the trial for the given household. As it is possible that different tradesmen carrying out the intervention may undertake the modifications in slightly different ways, with differing degrees of effectiveness, a stratum variable will also be included as a covariate that discriminates between participants in Taranaki and those in Wellington. For the main analysis drawing on additional data for Māori households from the HIPI study, the stratum variable will take a third level. As the unit of randomization, the household, is also the unit for which rates are estimated, there is no clustering to be accounted for in this analysis.

As with the HIPI study analysis, we will also analyze rates of specific injuries (specific to the intervention) for the treatment and control groups, expecting the safety effect to be stronger for these injuries than for fall injuries, as it was for the HIPI study.

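### The pooled model leaves out the known number of consenting participants in HIPI households; adding it for that stratum alone would recover a modest amount of precision at almost no cost

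*Protocol article*

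**What the plan says.** Section 3.2 plans two estimates of the fall rate: one from MHIPI alone, and one from MHIPI plus the Māori participants of HIPI. Section 3.3.2 calls the pooled one the main analysis.

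The two sources differ in what is known about exposure. In HIPI, "participants in the HIPI study consented to have the study team access their ACC injury records, which were assigned to individuals". In MHIPI, claims were matched anonymously to addresses, so "we cannot estimate fall injury rates per person-time as we have no adequate denominators".

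The HIPI data are brought to the MHIPI level: "To be consistent with the MHIPI data analysis", the "data for the Māori household members of the HIPI study will be aggregated to the household level".

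The model in 3.3.2 is a Poisson regression of household counts "with an offset that is the log of the length of the time interval over which the injury count was obtained". Its covariates are treatment, the household's fall count in the year before the trial, and stratum. In the pooled version "the stratum variable will take a third level", so HIPI has its own intercept. The same section reports that "the mean number of consenting participants per household from the HIPI study was 2.2 overall, 3.1 for Māori and 2.1 for non-Māori households".

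**The concern.** The missing denominator is a limitation of MHIPI, not of HIPI. A HIPI household's count can come only from its consenting members, so their number is the exposure behind the count. With log time as the only offset, two HIPI households with the same arm, follow-up and prior falls have the same expected count, whether one person or six contribute claims.

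Two things follow for the pooled estimate. Variation in household size stays in the residual and lowers precision. A chance difference between arms in participant numbers also enters the HIPI part of the rate ratio, except so far as prior falls absorb it.

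Consistency between the studies does not require this, because HIPI already has a separate intercept.

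**Working it through.** **No figure in the plan to reproduce.** The protocol gives no number for this choice. Its sample size (about 125 households per arm) does not bear on it.

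**1. Where the information is lost.** If each of n participants has a Poisson fall count with mean λt, the household total is Poisson with mean nλt. For a treatment given to the whole household, and with no person-level covariates, the total with log(n) + log(t) as offset carries all the information on the treatment effect. Aggregation therefore costs nothing; dropping n does.

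**2. Whether a HIPI-only term is compatible with pooling.** Write

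log E(y) = α(stratum) + β·arm + γ·prior falls + log t + δ·H·log n,

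with H = 1 in HIPI and 0 in MHIPI. Setting δ = 1 gives an offset; leaving δ free gives a covariate. The MHIPI linear predictor keeps its form, and the HIPI intercept is rescaled. β remains a common log rate ratio, provided that the effect is the same per household and per person.

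**3. Size of the HIPI stratum (assumed).** The means 2.2, 3.1 and 2.1 imply a Māori share of (2.2 − 2.1)/(3.1 − 2.1) = 10%, or 0–20% allowing for rounding. Section 4 reports 436 modified HIPI homes. If HIPI had 2 × 436 = 872 homes in total, that is about 87 households, or 174 at the upper end, beside about 250 in MHIPI.

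**4. Chance imbalance.** Assume an SD of household size of 1.45 (1 + Poisson with mean 2.1). The SE of the log ratio of mean sizes between arms is (1.45/3.1) × √(4/87) = 0.100, or (1.45/3.1) × √(4/174) = 0.071. With a more dispersed size distribution and 88 households it reached about 0.16.

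This imbalance applies to the HIPI stratum only. One simulation of the planned model gave SDs of the log rate ratio, pooled and HIPI-only, of 0.212 and 0.428 (87 households) and 0.118 and 0.189 (174 households). HIPI's weight is then about (0.212/0.428)² = 0.25 or (0.118/0.189)² = 0.39. A one-SE imbalance moves the pooled log rate ratio by about 0.25 × 0.100 = 0.025 or 0.39 × 0.071 = 0.028, before any adjustment through prior falls.

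**5. Precision.** The planned model was simulated with and without the HIPI size offset. There were 16 settings of 1,500 runs each, with no treatment effect. The settings crossed 88 or 174 HIPI households, 0.5 or 1.0 falls per household over 2.3 years, household frailty CV 0 or 0.8, and two size distributions with mean 3.1. Falls were proportional to size. Examples:

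| HIPI households | Falls per household | Frailty CV | Size distribution | Pooled SD, time only → with size | Pooled variance ratio | HIPI-only variance ratio |
|---|---|---|---|---|---|---|
| 88 | 0.5 | 0 | Poisson | 0.163 → 0.162 | 0.978 | 0.906 |
| 88 | 1.0 | 0.8 | dispersed | 0.158 → 0.157 | 0.989 | 0.852 |
| 174 | 0.5 | 0.8 | Poisson | 0.166 → 0.164 | 0.979 | 0.943 |
| 174 | 0.5 | 0 | dispersed | 0.156 → 0.149 | 0.915 | 0.789 |
| 174 | 1.0 | 0 | dispersed | 0.117 → 0.112 | 0.916 | 0.721 |

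Over all 16 settings:
- Pooled variance fell by 1–9%: about 2–9% without frailty and 1–4% with it. As a covariate the term gave about 2–9%.
- HIPI-stratum variance fell by about 6–28%.
- The mean log rate ratio was about 0 with and without the term.
- The model-based SE was the same to three decimals with and without the term.
- Type I error was 6.5–17% without the offset and 6–16% with it.

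Other simulations on similar assumptions gave HIPI-stratum reductions between about 3% and 35%. Their pooled reductions ran from nothing detectable to about 8% in most settings, with one at 14%.

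**The case against.** The strongest reply is that the plan is sound as it stands. The primary outcome is defined per household, and the household is the unit of randomization and of analysis. Using one unit in both studies is a legitimate choice, and prior falls partly stand in for size. All of this stands.

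It is also true that the pooled gain is small. A 9% cut in variance narrows the interval by 1 − √0.91 = 4.6%, and a 1% cut by 0.5%. Where household heterogeneity is large, the gain may be hard to tell from zero.

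The planned odds analysis in 3.3.3 offers further protection. It compares falls with other home injuries, so it largely cancels household size and can "control for age group, which was found to be an important factor in the analytical models". The article does not say whether HIPI data enter that analysis, and section 3.2 acknowledges that it uses less information than the rate analysis.

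A reader might infer more than the documents support:
- That collapsing the records to households in itself discards precision. Step 1 shows that it does not.
- That a 7–10% imbalance should be set against the 26% effect in the sample size statement. The imbalance is within HIPI, and it shifts the pooled estimate by under 3%. It is also part of the same sampling variance as the precision loss, so the two must not be added. The 26% refers to the percentage of households with falls, not to a pooled rate ratio.
- That the plan rules out age control outside the odds analysis. It says only that the odds analysis makes such control possible.

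What survives is narrow: a known exposure measure is left out of the main model, and the reason given does not require it.

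**Conclusion.** The point holds as a modest, inexpensive improvement. It is not an error that undermines the analysis. The omission is read from the model statement, which lists a time-only offset and no size term; the article does not say in words that participant numbers are discarded.

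The planned pooled estimate is unbiased under randomization. Leaving out the size term costs roughly 3–35% of variance within the HIPI stratum and about 0–9% of pooled variance in most settings. Because unscaled Poisson standard errors barely change when size is added, the cost appears as intervals slightly too narrow for the real variability, not as visibly wider ones.

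These ranges rest on assumptions outside the documents: the number of HIPI Māori households, the spread of household size, the fall rates, the heterogeneity between households, and falls proportional to size. Individual age in HIPI might add further precision, but the documents give no figure from which to judge this.

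**What to change.** Keep household counts and the household as the unit. In the pooled model, add log(number of consenting participants whose claims are counted in that household) for the HIPI stratum, set to zero for MHIPI households. A covariate is preferable because it does not force falls to be strictly proportional to size; an offset is the alternative. Report the time-only version as a sensitivity analysis.

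The participant number must match the people whose injuries are counted. Section 3.2 speaks of Māori household members, whereas the mean of 3.1 in 3.3.2 is per Māori household. The plan should say which applies. The number should be the one fixed at enrolment.

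The cost is one extra parameter on data already held. The MHIPI-only analysis is untouched, and the gain may turn out small. Residual overdispersion needs its own remedy, such as a robust or scaled variance.

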#### 3.2.2. Home Injury Claims Data for Participating Addresses

Injury counts will be obtained from ACC claims data for all home injuries, excluding deliberate injuries (assaults or self-harm), matched by the address fields of participants that we provide to ACC. Any form of matching has the potential for errors. Addresses in New Zealand are commonly specified in non-standardized forms that are difficult to match precisely. ACC have an identification number that is assigned to the claimant’s address, however it is not unusual for a given address to have more than one identification number, mainly arising from different ways that suburbs and towns are specified. This in turn is related to the number of different people in the household (each of whom may specify their address slightly differently to a given health provider). For the list of participants’ addresses we provided to ACC, they in turn furnished information on the number of ACC address IDs matched to the provided addresses, which was sometimes zero. One participating household’s address was matched to 24 ACC address IDs, which was clearly an error. This household will be excluded from any analyses (see Figure 1). There were a further eight households linked to two ACC address IDs, four linked to three IDs and one linked to five IDs. There is no feasibly mechanism by which the occurrence of multiple matches could be associated with the random assignment to intervention or control groups, which occurred after participants were recruited and visited. Multiple-matching of an intervention address could be expected to attenuate any intervention effect, as no change in injury risk can be expected for unmodified houses mistakenly classified as being in the intervention group.

Another form of matching error will arise where no match is made between a participant’s address and their ACC claims for home injury, because of errors in the specification of the addresses in either database. There were 35 participants’ addresses out of a total of 252 (14%) with no matching ACC claims, which provides an upper limit of the degree of such non-matching that occurred. Of these, 13 were in the intervention group. Some of these will not be in the ACC list of addresses because no occupant has had an injury resulting in an ACC claim while at that address. In the analyses, these households will be assumed to have zero injuries, including falls and specific injuries.

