#### 3.3.3. Odds of Fall Injuries

In the case of the sensitivity analysis of the odds of a home fall, the treatment effect will be estimated by the ratio of the odds of home fall injuries vs. other home injuries for the treatment group compared to the controls. We will use SAS regression procedures to calculate crude and adjusted odds ratios accounting for clustering at the individual and household level, such as GENMOD [11] with a REPEATED statement, which fits a GEE model to adjust standard errors for the effects of clustering. As we are analyzing the odds of fall injuries, we would expected some factors leading to correlations of injury rates within households, such as propensity to seek medical treatment, to have less of an effect (as they affect both numerators and denominators equally), leading to a smaller intraclass correlation coefficient (ICC).

An odds ratio less than one will indicate a safety effect from the intervention. We will also analyze the odds of specific injuries vs. non-fall home injuries using the same model specification.

This trial is registered, number ACTRN12609000779279.

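### The odds-ratio sensitivity analysis rests on an untested assumption about other home injuries, which the protocol's own text strains

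*Protocol article*

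**What the plan says.** **Outcomes.** Section 3.2 of the protocol article states "The primary outcome is rates of medically-treated unintentional falls per household per year". The secondary outcomes are specific injuries and "costs of both these types of injuries, due to falls generally or due to the specific injuries". Section 3.3.2 models household rates of falls and of specific injuries.

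**Use of other home injuries.** They appear only as the reference category of a sensitivity analysis. Section 3.3.3 defines the effect there as "the ratio of the odds of home fall injuries vs. other home injuries for the treatment group compared to the controls" and takes a value below one as showing that the package improves safety. Section 3.2 supports this by saying "it can be assumed that other types of injuries that occur in the home" "would be relatively unaffected by the intervention". The only reason offered is that the package was designed against falls. The same section gives a second argument: "Using an odds ratio as an outcome measure has the additional benefit of controlling for propensity to seek" treatment or be referred for it.

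**Text that bears on the assumption.** Section 3.1 says "Where needed, smoke alarms were also installed, but are not relevant to the outcome measure". Section 3.2.1 defines specific injuries as those the package might prevent, and includes some in which the person loses balance without ending on the ground: collisions with an object, and muscle, tendon or ligament strains.

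**Data.** Section 3.2.2 says "Injury counts will be obtained from ACC claims data for all home injuries", deliberate injuries apart, and 3.3.2 links the records to treatment arm.

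**The concern.** An odds ratio of falls against other injuries measures an effect on falls only if the package leaves the other injuries alone. If the package changes them, the ratio mixes the two effects, and the fixed reading in 3.3.3 assigns all of it to falls. That the package was designed to prevent falls is not evidence that it does nothing else.

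The article itself gives reasons for doubt. It places burns, strains and collisions among the injuries taken as little affected, yet it describes a package that included smoke alarms and an outcome class that treats some strains and collisions as preventable. At stake are the interpretation of the sensitivity analysis and, less directly, the net injury and cost picture. The trial is meant to inform a national programme, and the stated cost inputs cover fall and specific injuries only.

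**Working it through.** The plan gives no figure on this point, so there is none to reproduce. The check sets the passages side by side, then shows how the ratio behaves.

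**1. Passages compared**
- *Burns:* in the comparator (3.2). Smoke alarms were installed where needed in intervention houses during the modification period, and control houses went through the same process only after the study (3.1).
- *Strains and collisions:* in the comparator (3.2), but some are preventable by definition (3.2.1). They are not falls, so in the falls-versus-other ratio of 3.3.3 they count as other injuries.
- *Comparator for specific injuries:* all other treated home injuries in 3.2, but non-fall home injuries in 3.3.3. Under the first, falls that are not specific are in the comparator; under the second they are not. Read literally, the second also puts a specific injury that is not a fall in both classes.

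**2. Identity**
Let F and N be fall and non-fall counts and T household-time, by arm (t, c).

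OR = (F_t/N_t) / (F_c/N_c) = [(F_t/T_t)/(F_c/T_c)] / [(N_t/T_t)/(N_c/T_c)] = RR_fall / RR_non-fall

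This is exact for crude ratios and approximate for adjusted ones.

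**3. Numbers put in**
The fall rate ratio of 0.74 is the 26% reduction in the earlier HIPI trial (Introduction). The non-fall ratios are assumed.

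| RR_fall | RR_non-fall | OR |
|---|---|---|
| 0.74 | 0.80 | 0.93 |
| 0.74 | 0.90 | 0.82 |
| 0.74 | 1.00 | 0.74 |
| 0.74 | 1.10 | 0.67 |
| 0.74 | 1.20 | 0.62 |
| 1.00 | 1.10 | 0.91 |

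To see how large 0.90 is, suppose the package cuts only the specific non-fall injuries, by 26%. They would then have to make up 0.10/0.26 = 38% of the comparator. The share needed is smaller if the effect on specific injuries is stronger, as 3.3.2 expects.

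**4. Net effect**
With a share f of home injuries being falls (assumed), the all-injury rate ratio is 0.74f + RR_non-fall(1 − f). At f = 0.5 it is 0.87 if other injuries are unchanged, and 0.92 if they rise by 10%. The non-fall ratio that cancels the fall gain is 1 + 0.26f/(1 − f): 1.11, 1.17 and 1.26 for f = 0.3, 0.4 and 0.5.

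**5. Precision of a direct comparison**
Take 125 households per arm (3.2) and two years (Introduction). Assume a non-fall rate of 0.2 to 1.0 per household-year and an overdispersion factor φ of 1 to 2; the article gives neither. Events per arm are E = rate × 2 × 125 = 50 to 250, and SE(log RR) = √(2φ/E).
- Best case (E = 250, φ = 1): SE = 0.089, and the 95% CI multiplies or divides the ratio by exp(1.96 × 0.089) = 1.19.
- Worst case (E = 50, φ = 2): SE = 0.283, and the factor is 1.74.
- Power for a true 20% increase runs from 53% down to 9%. The smallest increase detectable with 80% power, exp(2.8 × SE) − 1, runs from 28% to 121%.

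**The case against.** The strongest reply is that the assumption supports only a sensitivity analysis. The household rates of falls and specific injuries, compared by randomised arm, do not use it. That stands, and it limits the point.

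A reader might go further and infer that harm, net effect and differential claiming would all go unseen. The documents do not support this:
- *Harm.* More falls would show in the primary outcome and more specific injuries in a secondary one. Only effects on other injuries are at issue.
- *No comparison at all.* Other injuries do enter a contrast between arms, as the denominator. Since both terms are planned, RR_non-fall is roughly recoverable as RR_fall/OR. A null fall rate ratio beside an odds ratio of 0.91 would give the problem away. The article does not state this check, however, and adjusted estimates match it only approximately.
- *Claiming.* Differences that act equally on all injury types cancel, as 3.2 says. Only differences specific to an injury type remain.
- *False benefit.* The mechanisms the article describes would lower the non-fall rate and move a protective odds ratio towards 1. Hardware that raises cuts or collisions is conceivable, but nothing in the text supports it.

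It is also fair that 3.2 says relatively unaffected rather than unaffected, and that a journal article may leave supportive tables to a fuller document. The absence of a non-fall rate table is therefore not the fault by itself. What stands is a stated assumption, and a reading rule resting on it, that sit badly with other stated text.

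Finally, the added comparison cannot serve as both a harm test and a clean negative control. If the package can alter other injuries, a ratio away from 1 does not say why. Separate reporting of burns would be sparser still and is not asked for.

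**Conclusion.** The point holds in limited form. The reading of the odds ratio in 3.3.3 depends on an assumption that is untested and is in tension with 3.1 and 3.2.1, and the comparator is not defined consistently between 3.2 and 3.3.3. Any effect on other injuries passes proportionally into the odds ratio, in either direction. With a fall rate ratio of 0.74, a 10% change in the non-fall rate moves it to 0.82 or 0.67. These sizes rest on assumed non-fall ratios, and the article gives no data on them. The bias that the text itself makes plausible is towards 1, which understates a benefit. The primary analysis is not touched. The case for change is that the stated reading can be checked cheaply on claims already obtained by arm.

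**What to change.** 1. In 3.2 and 3.3.2, add two supportive analyses with the existing household Poisson model, time windows, offset and covariates: the rate of home injuries that are neither falls nor specific, and the rate of all home injuries. Report rate ratios with 95% confidence intervals. Add the ACC cost of all home injuries as a further cost-benefit input.
2. In 3.2 and 3.3.3, replace the assumption and the automatic reading of a ratio below one with a statement that the odds ratio will be interpreted beside the fall and non-fall rate ratios.
3. Exclude specific injuries that are not falls from the odds-ratio comparator, use one comparator definition in 3.2 and 3.3.3, and reconcile 3.1, 3.2 and 3.2.1 on burns, strains and collisions.

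The cost is two reruns of an existing model on data already supplied, a cost total, and some rewording. The downside is two more supportive estimates with wide intervals. They cannot rule out modest harm, and a result near 1 must not be read as proof of no effect.
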